The primary endpoint is the failure proportion of the diagnostic strategy, defined as a diagnosed thrombo-embolic event at 3 months follow-up (either a PE or a deep venous thrombosis), among patients in whom PE was initially ruled out. Exclusion of PE in the ED is done upon a negative D-dimer result or negative CTPA or negative V/Q scan in both groups. The primary criterion of thrombo-embolic event will be based on an objective diagnosis of DVT on Doppler ultrasonography, an intraluminal defect on CTPA, or a V/Q lung scan with a reported high probability. To confirm the occurrence of the primary endpoint, all files with evidence of thrombo-embolic event collected by the local investigator of each center will be independently reviewed by an adjudication committee of three experts, emergency physicians, blinded one to each other, and blinded to the study period. The adjudication committee will also review cases of death with no evidence of thrombo-embolic event and will adjudicate the death as likely related to a PE or not. Adjudication of a PE-related death will follow the recommendations of Tritschler et al. [19]. The review process includes analysis of all medical files of the patient from inclusion to follow up, including reports of any imaging study.

Secondary endpoints include:
CTPA or V/Q scanAnticoagulant therapy administrationLength of stay in the ED (hours)Admission to the hospital following ED visitAll causes re-hospitalization at 3 monthsDeath from all causes at 3 monthsDiagnosed pulmonary embolism at 3-month follow-up, excluding the isolated sub-segmental pulmonary embolism, among patients in whom PE has been initially ruled outPulmonary Embolism Probability Score (PEPS)3-month total cost and cost-effectiveness (cost per major adverse event averted)

Details of PEPS are reported in Table 3 [18].

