### Sample size calculation

In the recent recommendations of the International Society of Thrombosis and Hemostasis on studies for PE diagnosis in the ED, it has been suggested that the maximum acceptable failure rate of a tested strategy should not exceed 1.85% [3]. The recent large European prospective cohort studies on PE diagnosis (PROPER, PERCEPIC, YEARS, ADJUST-PE) reported a failure rate of 0.1–0.5%. With an anticipated failure rate of 0.5% in the control group, a non-inferiority margin set at 1.35% (according to the ISTH recommendations so the upper bound of the 95% confidence interval (CI) of the failure rate in the intervention group will not exceed 1.85%), beta = 20%, and one-sided alpha = 2.5%, N1 = 857 patients are needed (East 6, Cytel, Cambridge, MA, USA). Under the assumption of an intra-class correlation coefficient (CCIC) of 0.018, an interperiod correlation (η) of 0.0115 (based on previous cluster randomized trials in French EDs) and a mean cluster size for one period (m) = 22 patients, the cluster design effect would be 1.37 [17, 20]. Considering 5% of non-evaluable patients, with 18 centers and two periods, 1234 patients are needed.

Besides the non-inferiority analysis, it is of utmost importance that the upper bound of the 95% CI of the failure rate of the tested modified diagnostic strategy remains below 1.85%, whatever the rate of the control group is. Our retrospective study reported an anticipated failure rate at 0.85% but focused only on low risk patients. Therefore, with an anticipated failure rate of 1% in the intervention period, the sample size of this group should be at least 700 to respect the maximal upper bound of 1.85%.

Therefore, for a conservative approach to these two conditions (non-inferiority margin at 1.35% and maximal upper bound of the 95% CI below 1.85%), 1400 (700 in each group) subjects will be needed in this study.

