Since this is a non-inferiority study, analysis of the principal criterion will be performed on the per-protocol population (patients without major protocol deviation as no respect of selection criteria, no respect of strategy assigned by randomization, missing values for the principal criteria, or other major protocol deviation identified during data review before freezing of the data base). A sensitivity analysis will be performed on the intention-to-treat population (all randomized patients, except those that withdrew consent). Given the rare occurrence of a thrombo-embolic (TE) event, a generalized linear regression mixed model with Poisson distribution (log link) will be performed (Poisson model for proportions), taking into account a random effect for each center and considering period and strategy-by-period interactions as fixed effects. The decision rule will be based on the upper bound of the 95% two-sided CI of the incidence rates ratio of TE events. Any missing value will be considered as a failure. Secondly, sensitivity analysis will be performed using the 95% two-sided CI of the difference of percentage of TE events between groups. If the upper bound of the CI is above 1.35% of the difference, the inferiority hypothesis of the intervention group will be rejected. Secondary criteria will be compared between groups on the intention-to-treat population and under the superiority hypothesis. The proportions of irradiative imaging, of introduction of anticoagulation regimen, of hospital admission following the ED visit, of all causes of hospital readmission at 3 months, and of all-cause death at 3 months will be compared between groups by using generalized linear regression mixed models with Poisson distribution (log link), taking into account a random effect for each center and considering period and strategy-by-period interaction as fixed effects. If the number of events is sufficient, generalized linear regression mixed modeling with Bernoulli distribution (logit link) will be performed. The proportion difference between groups and its 95% CI will be calculated.

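### The test rule for the 1.35% margin on the difference scale is written backwards and contradicts the sample size section

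*Protocol article*

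**What the plan says.** The endpoint is an unfavourable outcome. Objectives and outcomes: "The primary endpoint is the failure proportion of the diagnostic strategy, defined as a diagnosed thrombo-embolic event at 3 months follow-up", counted among patients in whom PE was initially ruled out. A higher proportion is worse.

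The Sample size calculation section plans with "a non-inferiority margin set at 1.35" percent. It ties the margin to an external ceiling, so that the "upper bound of the 95% confidence interval (CI) of the failure rate in the intervention group will not exceed 1.85" percent. It then adds a second condition, that "the upper bound of the 95% CI of the failure rate of the tested modified diagnostic strategy remains below 1.85" percent whatever happens in the control group.

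The Statistical analysis plan section gives two rules for the primary endpoint:

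- Main rule: "The decision rule will be based on the upper bound of the 95% two-sided CI of the incidence rates ratio of TE events". No ratio margin and no direction are attached to it.
- Second rule: "Secondly, sensitivity analysis will be performed using the 95% two-sided CI of the difference of percentage of TE events between groups". The next sentence gives the criterion: "If the upper bound of the CI is above 1.35% of the difference, the inferiority hypothesis of the intervention group will be rejected".

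**The concern.** In a non-inferiority test the null hypothesis is inferiority, here a MODS-minus-control difference of 1.35 percentage points or more. Rejecting it means concluding non-inferiority. With a failure endpoint this is justified only when the whole confidence interval lies below the margin, that is, when its upper bound is below 1.35%. The printed sentence rejects inferiority when the upper bound is above 1.35%.

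The trial was sized on the 1.35% difference, and this sentence alone turns that margin into a decision. If it is carried unchanged into analysis code or a results table, the difference-scale analysis would report a safety conclusion opposite to the data.

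**Working it through.** **1. Direction implied by the planning text**

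| Section | Quantity | Favourable to MODS when |
|---|---|---|
| Sample size calculation | Upper bound, MODS failure rate | does not exceed 1.85% (= 0.5% + 1.35%) |
| Sample size calculation, second condition | Upper bound, MODS failure rate | below 1.85% |
| Statistical analysis plan | Upper bound, difference | **above** 1.35% (as printed) |

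The third row runs against the first two.

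**2. Reproducing the stated sample size**

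Inputs from the Sample size calculation section: control rate 0.5% ("With an anticipated failure rate of 0.5% in the control group"), margin 1.35%, one-sided alpha 2.5%, power 80%. Assumption made here: the same 0.5% in the MODS group.

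n per group = (1.960 + 0.842)² × 2 × 0.005 × 0.995 / 0.0135² = 7.849 × 0.00995 / 0.00018225 ≈ 428.5

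Twice this is 857, the stated figure (858 if each group is rounded up to 429). With the stated design effect of 1.37, 857 × 1.37 = 1174. Then 1174 / 0.95 = 1236, or 1174 × 1.05 = 1233, against 1234 stated. The plan's figures therefore reproduce closely. The formula gives the power to find the upper bound *below* 1.35%, so the sample size presupposes the opposite of the printed rule.

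**3. What the printed rule does to example data**

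Upper bound = (p_M − p_C) + 1.96 × √[p_C(1 − p_C)/700 + p_M(1 − p_M)/700], with 700 per group and patients treated as independent.

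- 4 control, 4 MODS: p = 0.571% in each; difference 0; SE = √(2 × 0.005682/700) = 0.403%; upper bound 0.79%. The margin is met, but the printed rule does not reject inferiority.
- 4 control, 21 MODS: 0.571% and 3.000%; difference 2.429%; SE = √((0.005682 + 0.029100)/700) = 0.705%; upper bound 2.429% + 1.382% = 3.81%. The margin is missed, but the printed rule rejects inferiority.

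Multiplying each SE by √1.37 = 1.170 gives 0.92% and 4.05%, so both readings survive the protocol's own design effect.

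**4. Operating characteristics**

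These are exact binomial enumerations of the same Wald bound, without clustering. Entries are the probability of rejecting inferiority.

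| True rates, control vs MODS | n per group | Printed rule (above) | Corrected rule (below) |
|---|---|---|---|
| 0.5% vs 0.5% | 429 | 0.22 | 0.78 |
| 0.5% vs 0.5% | 700 | 0.08 | 0.92 |
| 0.5% vs 1.85% (at the margin) | 700 | 0.96 | 0.037 |
| 0.5% vs 3% | 700 | > 0.999 | < 0.001 |

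The corrected rule gives roughly the planned 80% power at 429 per group. At the margin its error is near the nominal 2.5%; the excess reflects the Wald interval at small counts.

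**The case against.** The strongest reply is about scope. A reader might infer that the trial's whole verdict is inverted, or that its type I error is 96%. The document does not support that. The reversed sentence belongs to the analysis introduced as a sensitivity analysis, and the main decision rests on the incidence rate ratio. That ratio rule has no stated margin. This is a different weakness, but it is why the difference-scale sentence carries the sized margin alone. The limit on scope stands.

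Second, the intended direction can be recovered from the Sample size calculation section, which also contains a correctly directed requirement on the MODS group alone. The sentence is probably a drafting slip, and a statistician would be unlikely to apply it literally. This lowers the practical risk but does not make the text right. The single-group requirement concerns the MODS failure rate, not the difference.

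Third, examples close to the margin are fragile. With 3 control and 6 MODS events per 700, the upper bound is 1.27% for independent patients but 0.429% + 1.96 × 0.427% × √1.37 = 1.41% with the stated design effect. Also, the analysed denominator will be below 700, because it is per protocol and limited to patients with PE ruled out. The examples above are therefore illustrations only; the argument about direction needs none of them.

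Fourth, the full plan in Supplementary file 2 was not available here and may word the rule correctly. In that case the article and the plan conflict.

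No alternative reading rescues the sentence. If the difference were control minus MODS, the relevant limit would be a lower bound against −1.35%. If the word meant was non-inferiority, the print is still wrong, and that repair leads to the same direction.

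**Conclusion.** The point holds for the difference-scale rule: as printed it is reversed and contradicts the protocol's own sample size section. Read literally, that analysis would reject inferiority with probability about 0.96 when MODS sits at the margin, and about 0.08 when both strategies fail at 0.5%. The corresponding figures for the corrected rule are about 0.04 and 0.92. These probabilities assume 700 independent evaluable patients per group and an unpooled Wald interval; the error of direction depends on neither assumption. It does not follow that the main conclusion, based on the rate ratio, is inverted. The sentence must still be corrected, because it is the only stated test decision on the margin for which the trial was sized.

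**What to change.** Replace the sentence with: If the upper bound of the two-sided 95% CI of the difference (MODS minus control) is below 1.35%, the inferiority hypothesis is rejected and non-inferiority is concluded.

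Before the database is frozen, check that the full statistical analysis plan states the same direction and the same order of subtraction, and correct it if it does not. The cost is one sentence, with no change to sample size, data collection or conduct.

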### Procedure and interventions

The diagnostic strategy for PE will first include a D-dimer analysis. The threshold for ruling out PE before ordering an imaging study will depend on the study period; in the control period, a positive D-dimer is defined as > 500 ng/ml in patients aged 50 years and younger, and as > age × 10 ng/ml for patients older than 50 years.

In the intervention period, the YEARS score will be assessed (Table 2). If the YEARS score is 0 (absence of any of the three items), a positive D-dimer is defined as > 1000 ng/ml. In other cases, the threshold will remain unchanged (> 500 ng/ml in patients aged 50 years and younger, and as > age × 10 ng/ml for patients older than 50 years).

**Table 2 Tab2:** YEARS rule, 0–3, one point for each positive item

Hemoptysis	+ 1 point
Clinical signs of DVT	+ 1 point
PE is the most likely diagnosis	+ 1 point

*DVT* deep venous thrombosis, *PE* pulmonary embolism

The total duration of a patient’s participation in the study is 3 months.

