### Objectives and outcomes

The primary objective of this trial is to assess the safety of a modified diagnostic strategy (MODS) in the ED using the YEARS rule for patients in whom PE is not excluded by PERC score. Secondary objectives are to assess the efficacy of the MODS strategy in reducing ordering of CTPA or V/Q scan, introduction of anticoagulant, ED length of stay, hospital admission following ED visit, all causes readmission and mortality at 3 months, and diagnosed pulmonary embolism at 3 months after excluding isolated sub-segmental PE. The trial will also assess the safety of the PEPS score (Table 3) and evaluate the overall 3-month cost-reduction of the MODS strategy [18].

**Table 3 Tab3:** Pulmonary Embolism Probability Score (PEPS)

	Points
Age < 50 years	−2
Age 50–64 years	−1
Chronic respiratory disease	−1
Heart rate < 80/min	− 1
Chest pain and dyspnea	1
Prolonged decubitus	2
Sex male	2
Syncope	2
History of thrombo-embolic disease	2
Estrogen use	2
SpO2 < 95%	3
Lower leg pain or edema	3
Pulmonary embolism is the most likely diagnosis	5

< 0 Pulmonary embolism (*PE*) unlikely (PE ruled out) ; 0–4, low probability (D-dimer threshold at 1000 ng/ml) ; 5–11, intermediate probability (age-adjusted threshold for D-dimer) ; > 11, high probability (computed tomographic pulmonary angiogram indicated)

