The ED length of stay will be compared between the two periods using a linear regression mixed model, taking into account a random effect for each center and considering period and strategy-by-period interaction as fixed effects. In case of non-normality distribution of the interest variable, a transformation could be performed or a model appropriate to data distribution could be selected.

Differences between groups in the proportion of patients with diagnosed PE at 3-month follow-up, excluding isolated sub-segmental PE, among patients in whom PE has been initially ruled out, will be calculated as well its 95% CI. If possible, generalized linear regression mixed models with Poisson distribution (log link) will be performed. A random effect for each cluster will be considered and considered fixed effects will be period and strategy-by-period interactions. If the number of events is sufficient, generalized linear regression mixed modeling with Bernoulli distribution (logit link) could be performed. The proportion of patients with a diagnosed TE event at 3-month follow-up (either a PE or a deep venous thrombosis), among patients in whom PE was initially ruled out by the PEPS score, will be described with its 95% CI.

Sensitivity analysis will be performed on the per-protocol population. Missing values for secondary criteria will not be replaced. All superiority tests will be two-sided and *p* values less than 0.05 will be considered significant.

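### The per-protocol sensitivity analysis of CTPA or V/Q imaging selects patients on the imaging outcome and is biased toward a reduction under MODS

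*Protocol article*

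**What the plan says.** All points are from the protocol article.

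- **Strategy (Procedure and interventions).** "The threshold for ruling out PE before ordering an imaging study will depend on the study period". Under control, a result counts as positive above 500 ng/ml up to age 50, and above an age-adjusted value after that. Under MODS: "If the YEARS score is 0 (absence of any of the three items), a positive D-dimer is defined as > 1000 ng/ml". With one or more YEARS items, the control threshold applies in both periods.
- **Endpoint (Objectives and outcomes).** "CTPA or V/Q scan" heads the list of secondary endpoints, and reducing such imaging is the first-named secondary objective.
- **Main analysis (Statistical analysis plan).** "Secondary criteria will be compared between groups on the intention-to-treat population and under the superiority hypothesis". Imaging comes first among the proportions to be compared: "The proportions of irradiative imaging, of introduction of anticoagulation regimen, of hospital admission following the ED visit".
- **Per-protocol population (same section).** It is introduced for the primary criterion. One of its listed major deviations is "no respect of strategy assigned by randomization".
- **Sensitivity analysis (same section).** "Sensitivity analysis will be performed on the per-protocol population". The sentence directly follows the secondary analyses, and the next one deals with missing secondary values. The primary criterion is already analysed per protocol, so this sentence can only concern the secondary criteria. Imaging is not exempted.

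**The concern.** The two strategies give different instructions only for patients with YEARS 0 and a D-dimer above the control threshold but not above 1000 ng/ml (the window). In the window, respecting MODS means no imaging and respecting control means imaging. Removing patients whose strategy was not respected therefore removes imaged window patients from the MODS group and non-imaged window patients from the control group. For the imaging endpoint, the exclusion criterion is the outcome.

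What is left mainly describes how D-dimer values and YEARS scores are distributed, and says little about whether physicians ordered fewer scans. Less imaging is the main practical benefit expected of MODS. A reader who sees a reduction in both populations may take the second as confirmation, although selection alone would tend to produce it.

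**Working it through.** The article gives no expected figure for imaging, so there is none to reproduce. The check is algebra, followed by illustrations on stated assumptions.

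**Inputs**
- From the article: 700 patients per group (Sample size calculation); two-sided 0.05 for superiority tests (Statistical analysis plan); the thresholds and the exclusion clause cited above.
- Assumed, because the article does not give them: *w*, the share of patients in the window; *h*, the share positive under both rules; how often window patients are imaged.

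**Direction of the bias**

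Let *A* be the share imaged and above both thresholds, *B* the share not imaged and below both, and *r* the probability of imaging in the window. Take *A*, *B*, *w* and *r* as equal in the two periods, so that MODS changes no imaging decision. The retained patients give:

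- MODS: A / (A + B + w(1 − r))
- Control: (A + wr) / (A + B + wr)

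The first is at most A/(A + B), and the second is at least A/(A + B). With *A*, *B* and *w* above zero, at least one inequality is strict for any *r*. The expected per-protocol rate is therefore lower under MODS although the true difference is 0. In 200,000 random settings of these quantities, the difference was never zero or positive.

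**Size when physicians image every window patient in both periods** (r = 1, full adherence elsewhere)

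- Intention-to-treat: h + w in both periods, difference 0.
- Per-protocol: MODS h/(1 − w), control h + w, difference −w(1 − w − h)/(1 − w).
- w = 0.10, h = 0.30: 0.30/0.90 = 33.3% (630 patients kept) against 40.0% (700 kept), or −6.7 points; p is about 0.012 in a simple test that ignores clustering.
- Smallest over w = 5–20% and h = 20–40%: w = 0.05, h = 0.40 gives 0.40/0.95 − 0.45 = −2.9 points.
- Largest: w = 0.20, h = 0.20 gives 0.20/0.80 − 0.40 = −15.0 points.

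**Size when MODS is partly taken up**

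Let *u* be the share of MODS window patients managed as assigned, with control fully adherent. The intention-to-treat difference is −wu. The per-protocol difference is h/(1 − w(1 − u)) − (h + w). With w = 0.10 and h = 0.30:

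| Uptake u | Intention-to-treat | Per-protocol | Inflation |
|---|---|---|---|
| 0 | 0.0 | −6.7 | 6.7 points |
| 0.5 | −5.0 | −8.4 | 3.4 points |
| 0.8 | −8.0 | −9.4 | 1.4 points |

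**A second set of assumptions**

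With 25% above both thresholds, r = 0.9 in both periods and no true effect:

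- w = 5%: 26.2% against 29.6% (−3.5 points before rounding of the rates)
- w = 10%: 27.5% against 34.3% (−6.9 points before rounding), with about a 77% chance of p < 0.05 if clustering is ignored
- w = 20%: 30.5% against 43.9% (−13.4 points)

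If no window patient is imaged in either period (r = 0) and w = 10%, the result is 25.0% against 27.8% (−2.8 points). Adding 5% off-protocol imaging decisions outside the window in both periods changes these differences by less than 1 point.

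**The case against.** The strongest reply is that the imaging claim already rests on the intention-to-treat comparison, and nothing in the article lets a per-protocol result replace it. This stands. The flaw is confined to a supportive analysis.

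Other replies narrow the point:

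- **The exclusion rule is partly inferred.** The article does not say that every imaging decision against the threshold is a major deviation, and the full analysis plan is not shown. However, the article defines the strategy only through that threshold, names failure to respect it as a major deviation, and exempts no endpoint.
- **The direction needs equal case mix.** Treating physicians recruit during a period they know, so the D-dimer and YEARS mix may differ between periods, by selection or by chance. A reader might infer that the per-protocol result must show a reduction. The algebra supports a bias toward one, not a guaranteed observed sign.
- **The largest sizes are extreme.** They assume no uptake of MODS in the window and full adherence elsewhere, and the window shares are not in the article. At 80% uptake the distortion is modest.

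A reader might also infer that the per-protocol analysis can never disagree with intention-to-treat, or that it conceals poor uptake. Neither follows. At zero uptake the two differ (0 against −6.7 points), intention-to-treat shows no effect, and the gap itself points to non-adherence. Nor do the documents support extending the point to ED length of stay: a link through imaging is plausible, but no size can be derived.

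**Conclusion.** The point holds in a limited form. As written, the plan includes an imaging analysis whose population depends on imaging, and that selection favours MODS. Under equal case mix and the plain reading of the exclusion clause, the direction of the bias holds for any window share above zero. Its size cannot be fixed from the article: −2.9 to −15.0 points is the illustrative range at zero true effect, falling to about 1.4 points of inflation at 80% uptake in the example. The quoted p-value and chance of significance ignore clustering, which affects them but not the bias. The analysis therefore gives no independent support for a reduction in imaging. The intention-to-treat comparison remains the main analysis and is sound on this point, and no conclusion drawn from it needs to change.

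**What to change.** In the Statistical analysis plan section, where the per-protocol repeat of the secondary criteria is announced, do one of the following for the CTPA or V/Q endpoint:

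- exclude it from the per-protocol sensitivity analysis; or
- define its sensitivity set by breaches of the selection criteria only, which are judged before imaging.

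In either case, report by group the proportion imaged although below the assigned threshold and the proportion not imaged although above it. This shows uptake directly.

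The cost is about one sentence and, under the first option, one fewer supportive analysis. The adherence table needs each patient's D-dimer value. The article's summary of the e-CRF names decision-rule items but not that value, so the sponsor should confirm that it is recorded. No clinical rule changes.
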